### Data monitoring

Based on pre-pilot studies we do not anticipate risks to participant safety as a direct result of the study. We will not be conducting any interim data analysis and will not convene a separate Data Monitoring Committee. The trial may be prematurely discontinued by the sponsor, REC or chief investigator (with the agreement of the sponsor and the REC) on the basis of new safety information or for other reasons given by the sponsor or the REC. As the study is a small pilot, we will not convene a Trial Steering Committee. The study will be subject to the standard local and national governance frameworks of the sponsor, the Promoting Recovery Services and research coordination, the clinical research network and the REC.

### Data management

We will use paper assessment packs and enter data into electronic databases which include: (1) baseline demographics, (2) repeated clinical measures, (3) sessional therapy measures and (4) therapy delivery and adherence. Outcome assessments will be carried out by researchers who do not have access to therapy or feedback data. Data will be checked and cleaned against original paper copies and a final database returned to the statistician, who will combine with allocation data for analysis.

Patient data will be pseudonymised for the duration of the study and fully anonymised thereafter. Fully identifiable personal details will be kept on paper in a locked filing cabinet in a locked or occupied office; on secure NHS computers; and encrypted on password-protected computers. All trial data will be stored in line with the Data Protection Act [30].

The allocation database will be accessible only to the study randomiser (who will not conduct post-baseline assessments) and the trial statistician until the study is completed.

### Safety monitoring and adverse event reporting

We do not anticipate safety concerns arising as a direct result of the therapy, which is usually perceived as helpful by service users. However, we will monitor adverse events, defined as any deterioration in psychosocial functioning, irrespective of severity, carefully as one of our outcomes. All adverse events will be reported to the clinical team to ensure adequate care, and will be documented by the study team. Events considered by the participant, clinical service or research team to be unexpected and related to the study will be reviewed for seriousness. Serious adverse events that are related to the trial will be reported to the trial sponsor and the REC within 15 days.

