**Methods:**

The Balancing ACT study is a randomised controlled trial comparing Balancing ACT groups (ACT/PE) plus routine care to routine care alone. Balancing ACT (ACT/PE) comprises ten group sessions, each lasting 2 hours, delivered weekly. The primary outcome is psychological wellbeing; secondary outcomes are mental health relapses (measured by service use averages for the 12 months pre baseline and 3 months post baseline). We will also measure mood, distress, recovery and psychological change processes. Participants will be randomised in a 1:1 ratio, after baseline assessment. Outcomes will be assessed by trained assessors blind to treatment condition at 0, 10 and 14 weeks. Recruitment began in April 2017 and is on-going until the end of October 2017.

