### Study design

Balancing ACT is an RCT with random allocation to one of two arms, comparing our active intervention (ACT/PE + TAU) to routine care alone (TAU). TAU will be delivered without interference in both conditions and includes care coordination, medication, and practical/emotional support for the individual. We will record what is delivered as TAU. Assessments will take place at baseline (0 weeks), 10 weeks (post therapy) and 14 weeks (post-booster session). After 14 weeks, TAU participants will be offered the intervention. Trained research workers will complete assessments with participants. Baseline assessments will be carried out prior to randomisation; 10- and 14-week assessments will be arranged by the trial research worker, but carried out by a different assessor, who will be blind to treatment allocation. Service measures [19] will be completed for the 12-month period before baseline and 3 months after the final baseline assessment. The study design is illustrated in Fig. 1.

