#### Intervention

The ACT/PE intervention will consist of ten groups, each running over ten consecutive weeks, followed by a booster session, 4 weeks later. Each group session will last for 2 h. The intervention will be delivered in addition to routine care (specialist care coordination, medication, practical and emotional support), and will be compared to routine care alone (TAU). After the 14-week assessment, individuals in the routine care condition will be offered the intervention.

The ACT/PE intervention will focus on psychoeducation approaches to understanding bipolar and mood disorders. Each session will focus on a different issue pertinent to bipolar disorder; including, mania, stress, sleep, depression, medication, communicating with friends and family, and relapse prevention. Each session will introduce ACT skills as a different way of responding to symptoms of bipolar disorder. The Balancing ACT groups are designed to be interactive with experiential exercises throughout and a commitment to work towards a valued goal, and the practice mindfulness exercises in between sessions.

We acknowledge that 14 weeks is a relatively short timeframe to assess change. For the pragmatic purposes of this study, because we are interested in the potential helpfulness of the intervention, rather than the longevity of the effects, we consider this time period appropriate. ACT has been shown to achieve change in brief interventions: previous studies from our research group [20] have shown significant change in 12 weeks during ACT interventions with clients with psychosis. This is longer than ACT interventions would normally be, but consistent with psychoeducation groups for people with bipolar disorder [6–8]. A future study can address maintenance of effects over time.

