### Measures

#### Outcome and timeline

Following informed consent from each participant, all outcomes will be assessed by a trained study researcher. Demographic/clinical characteristics (age, gender, ethnicity, diagnosis) will be assessed at baseline. Outcomes will be assessed at baseline (0 weeks), then at 10 weeks and 14 weeks post randomisation (Table 1).

**Table 1 Tab1:** Balancing ACT: evaluating the effectiveness of psychoeducation and Acceptance and Commitment Therapy (ACT) groups for people with bipolar disorder: Study protocol for a pilot randomised controlled trial. List of measures

	Completed at:
Service user measures	
Brief Quality of Life in Bipolar Disorder (Brief QoL.BD: Michalak and Murray, 2009) [21]	1, 2, 3
Clinical Outcomes in Routine Evaluation Measure (CORE-10; Barkham et al., 2008) [25]	1, 2, 3
Valuing Questionnaire (VQ8; Smout et al., 2014) [27]	1, 2, 3
Acceptance and Action Questionnaire-II (AAQ-II; Bond et al., 2011) [28]	1, 2, 3
Southampton Mindfulness Questionnaire (SMQ; Chadwick et al., 2008) [29]	1, 2, 3
Bipolar Recovery Questionnaire (BRQ; Jones et al., 2013) [26]	1, 2, 3
Internal States Scale (ISS; Bauer, 1991) [24]	1, 2, 3
Researcher-rated measure	
Client Service Receipt Inventory (CSRI; Beecham and Knapp, 2001) [19] for the 12 months preceding and 3 months following baseline	1, 3
Service use (average/month) in preceding 12 months and following 3 months from baseline	
Sessional measures	
Brief Quality of Life in Bipolar Disorder (Brief QoL.BD: Michalak and Murray, 2009) [21]	Sessional

Key: Completed at: 1 = baseline (0 weeks), 2 = post therapy (10 weeks); 3 = post follow-up (14 weeks)

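### Adverse events of any severity are an outcome, but after randomisation the study team sees ACT/PE participants on about 11 to 13 occasions and TAU participants on two, so minor events tend to be found unequally

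*Protocol article*

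**What the plan says.** **Definition and recording.** Protocol article, Safety monitoring and adverse event reporting: "we will monitor adverse events, defined as any deterioration in psychosocial functioning, irrespective of severity, carefully as one of our outcomes". The same section continues: "All adverse events will be reported to the clinical team to ensure adequate care, and will be documented by the study team". A filter follows, but only for seriousness: "Events considered by the participant, clinical service or research team to be unexpected and related to the study will be reviewed for seriousness". It does not narrow the any-severity outcome.

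**Contacts after randomisation.** For the intervention arm, the Abstract (Methods) states: "Balancing ACT (ACT/PE) comprises ten group sessions, each lasting 2 hours, delivered weekly". The Intervention section adds a further contact: "followed by a booster session, 4 weeks later". For both arms, Outcome and timeline states: "Outcomes will be assessed at baseline (0 weeks), then at 10 weeks and 14 weeks post randomisation". Under Study design, TAU participants are offered the groups only once the 14-week point has passed, so they have no sessions during follow-up.

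**What happens at sessions.** Under Therapists, a study-team member works alongside the service's own therapists. Mood is rated at sessions (Other clinical outcomes), and so is the Brief QoL.BD (Table 1).

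**Record-based measures.** Admissions, inpatient days, and crisis-team contacts and days are taken from medical records in both arms (Secondary outcomes; Service use and costs).

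Table 1 lists no adverse event measure. No section sets common times or a look-back period for eliciting events.

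**The concern.** The Background describes a recurrent illness with residual symptoms and relapse rates of 40 to 60%. If even slight worsening counts, many qualifying events belong to the natural course, and the number recorded depends partly on how often someone is there to notice. A high threshold such as admission would be largely immune to this, because records reveal it whatever the contact schedule. A threshold with no lower limit is not.

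The extra observers are also unblinded. Session staff know the allocation, whereas the 10- and 14-week assessors are meant to be blind to it and have no access to therapy data.

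An excess of minor events in ACT/PE would then be hard to read. It could be ordinary fluctuation mistaken for harm, or a real signal dismissed as extra observation. The article plans no separate data monitoring or steering committee that might weigh this, and the results are meant to inform a larger evaluation. An analysis plan could not repair the imbalance afterwards, because TAU events that nobody asked about leave nothing to analyse.

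**Working it through.** The article states no adverse event rate, and its sample size of 36 is set by resources, so there is no stated figure to reproduce. The contact counts come from the text. Every event rate, recall period and reporting share below is an assumption.

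**Step 1: occasions.** ACT/PE: 10 sessions + 1 booster + 2 assessments = 13 scheduled contacts. Session ten falls near the 10-week assessment and the booster near the 14-week one, so there are 13 − 2 = 11 distinct occasions. TAU: 2. The ratio is 13/2 = 6.5, or 11/2 = 5.5.

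**Step 2: independent dips, no recall, no true difference.** Let p be the chance that a reportable event is seen at any one contact, equal in both arms. With k contacts, P(at least one recorded event) = 1 − (1 − p)^k.

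| p | ACT/PE, k = 13 | ACT/PE, k = 11 | TAU, k = 2 | Risk ratio, 13 v 2 | Risk ratio, 11 v 2 |
|---|---|---|---|---|---|
| 3% | 33% | 28% | 6% | 5.5 | 4.8 |
| 5% | 49% | 43% | 10% | 5.0 | 4.4 |
| 10% | 75% | 69% | 19% | 3.9 | 3.6 |

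For example, at p = 5%: 1 − 0.95^13 = 0.487, 1 − 0.95^2 = 0.0975, and 0.487/0.0975 = 5.0. With 36/2 = 18 per arm and 13 v 2 contacts, the chance that a two-sided Fisher test reaches p < 0.05 against ACT/PE is 65% at p = 5% and 92% at p = 10%.

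**Step 3: incomplete attendance.** If a share a of the 11 sessions is attended, k = 2 + 11a. At a = 0.7, k = 9.7 and the risk ratio is 4.0 (p = 5%) or 3.4 (p = 10%). At a = 0.5, k = 7.5 and it is 3.3 or 2.9.

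**Step 4: lasting episodes, recall and care-team reports.** A weekly simulation used an onset risk of 5% per week and a mean episode duration of 1.5 or 4 weeks. Participants were observed at weeks 1 to 10 and 14 in ACT/PE, and at weeks 10 and 14 in TAU. Each cell gives the risk ratio for any recorded event, for 1.5-week then 4-week episodes.

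| Recall at each contact | Care team reports none | Care team reports half | Care team reports 90% |
|---|---|---|---|
| None | 3.4; 2.0 | 1.4; 1.3 | 1.05; 1.04 |
| 4 weeks | 1.4; 1.3 | 1.15; 1.12 | 1.02; 1.02 |
| Whole interval | 1.0; 1.0 | 1.0; 1.0 | 1.0; 1.0 |

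The first row and column correspond to 46% v 13% and 54% v 27% of participants. In no scenario did the expected bias favour ACT/PE.

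**Step 5: after the fix.** Comparing only what the two common assessments find gives k = 2 in each arm and a risk ratio of 1.0 in the step 2 model. Whole-interval recall gives 1.0 in the simulation.

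**The case against.** The strongest reply is that the route of collection is not stated. The article does not say that adverse events are gathered at sessions, or that TAU participants are asked without look-back, and a journal article may leave event forms to the full protocol. Its general rule even points towards common visits: outcomes are assessed by a trained researcher at set times, and outcome assessors cannot see therapy data. This limits what can be said about size. It does not remove the point. Table 1 contains no adverse event measure, and the safety section has the study team document all events, not only those that surface at assessments.

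Routine care continues in both arms, and participants or the clinical service may raise events. That stands and shrinks the ratio, as step 4 shows, but it does not reverse it.

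The Statistical analysis section names no adverse event rate or test. That also stands, so the Fisher figures only illustrate a test that might be applied. An outcome of a two-arm randomised trial will still be set out by arm, at least descriptively.

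A reader might infer two stronger things, and the documents support neither:

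- **That mood swings noted at sessions are themselves adverse events.** The criterion is psychosocial functioning. The sessional mood scale is a separate measure, and no text turns a mark on it into an event.
- **That the pilot cannot inform on safety.** Admissions and crisis-team use come from records over the same period in both arms, and distress, mood and quality of life are measured at the same visits in both.

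**Conclusion.** The point holds as a tendency. The definition, its standing as an outcome and the contact counts are all in the article, and together they favour finding minor events in ACT/PE. It would go too far to say that ACT/PE will look more harmful, because that depends on how events are elicited.

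The assumed range is wide. The risk ratio is 1.0 if both assessments recover the whole interval, about 1.3 to 1.4 with four-week recall and no care-team reports, 2.0 to 3.4 for lasting episodes with neither, and about 4 to 5.5 for independent dips with full attendance and no recall. The upper end is close to a worst case. The problem is confined to minor events, and it should be settled before data collection, when it is cheap to do so.

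**What to change.** Add to Safety monitoring and adverse event reporting:

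- Any between-arm comparison of adverse events uses events elicited identically in both arms: one standard set of questions covering the whole interval since the last visit, asked at the existing 10- and 14-week assessments, plus the record review already planned for service use.
- The source of each event is recorded (assessment, records, session, care team or participant).
- All events are reported by arm, with session-detected events listed separately. They are still documented and passed to the clinical team as now.

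The cost is a short question set at two existing visits and one extra field on the event form, with no added visits or participants. The downside is that the compared rate omits minor events seen only at sessions, including any that the group itself provokes. Those events must therefore be reported alongside the compared rate and not dropped.

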## Background

Bipolar disorder is a chronic and disabling psychiatric condition, characterised by recurrent episodes of mania, hypomania and depression. It places a heavy burden on sufferers and families, and has high societal and healthcare costs [1, 2]. An estimated 2 to 6% of the general population in the UK meet the criteria for bipolar disorder, costing £5.2 billion annually in healthcare and lost employment [3]. Many of the service users with a diagnosis of bipolar disorder also experience prominent psychotic symptoms, with differential diagnoses of schizoaffective disorder, and relapses characterised by repeated manic psychotic episodes and grandiosity. Such presentations require specific adaptations to standard psychological interventions for bipolar disorder in order to address psychosis, alongside mood regulation, with a particular emphasis on impulsivity, irritability, disinhibition and elation [2].

The main treatment offered for bipolar disorder is medication [2]. Despite this, many individuals continue to experience residual symptoms, even when they are fully concordant with medication, with rates of relapse of between 40 and 60% [2, 4, 5]. Psychological therapies were previously thought to add little to the treatment of severe mental illness. However, psychological interventions for people with psychosis are now firmly established as clinical and cost-effective interventions, and, although the move away from a predominantly medical approach has been more recent for bipolar disorder, there is increasing evidence that patients benefit from high-quality psychological therapies, with clinical and cost effects, as well as improving the quality of life of service users and their families [6]. The National Institute for Health and Care Excellence [2] guidelines recommend up to 16 sessions of individual cognitive behaviour therapy (CBT) including psychoeducation and self-management/relapse prevention for bipolar disorder and the same duration of intervention for people with psychosis, incorporating self-monitoring, coping strategies, distress-reduction and improving functioning. Family Interventions (FI) and psychosocial/vocational support are also recommended for both bipolar disorder and psychosis.

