#### Secondary outcomes

The proposed secondary outcome of service use will be assessed from the medical records for the 12 months preceding entry to the study and the 3 months during the trial. We will calculate the number of admissions to hospital and contacts with the crisis/home treatment team as well as days under each of these services as an average per month. This is an indication of the severity of the presentation and the cost to the service of care.

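### Adverse events are defined by decline in psychosocial functioning alone, so a death, injury or act of self-harm need not be recorded as one, and admissions counted as service use are not linked to the harms record

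*Protocol article*

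**What the plan says.** The section Safety monitoring and adverse event reporting monitors "adverse events, defined as any deterioration in psychosocial functioning, irrespective of severity", "carefully as one of our outcomes". All adverse events are passed to the clinical team and documented by the study team. Two further sentences deal with seriousness: "Events considered by the participant, clinical service or research team to be unexpected and related to the study will be reviewed for seriousness", and "Serious adverse events that are related to the trial will be reported to the trial sponsor and the REC within 15 days". The article gives no other definition of an adverse event and no criteria for seriousness.

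The Background describes the population as having "relapses characterised by repeated manic psychotic episodes and grandiosity", and bipolar disorder under medication as continuing "with rates of relapse of between 40 and 60" per cent, with no period attached to that figure.

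Relapse is handled as an efficacy outcome. The abstract's Methods paragraph says "secondary outcomes are mental health relapses (measured by service use averages for the 12 months pre baseline and 3 months post baseline". Secondary outcomes specifies "the number of admissions to hospital and contacts with the crisis/home treatment team as well as days under each of these services", expressed as an average per month.

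**The concern.** A definition of adverse event decides what enters the harms record. Here the duties to document an event and to inform the clinical team attach to the defined term, and the term covers functioning only. A brief, mild social setback qualifies, because there is no threshold. A death, a fracture, or an act of self-harm followed by return to usual functioning does not clearly qualify.

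Three things are at stake. First, the article makes adverse events an outcome, so the definition fixes what that outcome measures. Second, under Data monitoring, new safety information is a ground for ending the trial early, and there is neither a separate Data Monitoring Committee nor a Trial Steering Committee; the adverse-event record is the main safety information that the trial itself generates. Third, the Discussion foresees a larger evaluation if the pilot goes well, and its harms experience would be carried into that application. An event that was never recorded as a harm cannot be graded later.

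**Working it through.** No calculation tests this point, since it turns on the wording of a definition. The check is to apply the wording to each type of event and then ask whether another part of the article fills the gap.

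**Step 1. Apply the definition literally.**

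| Event | Adverse event on the wording? |
|---|---|
| Mild, short-lived social decline | Yes, as severity is irrelevant |
| Manic or psychotic relapse with evident loss of functioning | Yes, though not named |
| Worsening of mood or psychotic symptoms with functioning so far held | Only if a rater also judges functioning to have declined |
| Self-harm followed by return to usual functioning | Not named; depends on the rater |
| Physical injury | Not unless recorded as a functional decline |
| Death from any cause | Not unless recorded as a functional decline |
| Psychiatric admission or crisis-team episode | Not by itself; no link is stated |

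**Step 2. Do the seriousness sentences repair it?** No. They give no criteria, such as death or admission, that would bring an event in by another route. They also narrow further: review for seriousness is reserved for events thought both unexpected and related, and onward reporting for serious events that are related. A serious event thought unrelated, or expected in this population, is not assessed for seriousness under these sentences.

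**Step 3. Do the other outcomes repair it?** Only in part.

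- *Service use* (Secondary outcomes; Service use and costs) captures admissions and crisis care from records, but as monthly averages. It does not capture relapse that never reaches those services, nor physical events.
- *Mood and distress* (Other clinical outcomes) are measured at 0, 10 and 14 weeks. The sessional mood scale is tied to therapy sessions, which the routine-care arm does not attend during the comparison. Neither is a record of events.
- *Linkage*: no sentence says that an admission found in the record search becomes an adverse event. One admission can therefore stand in the service-use outcome and be absent from the harms record.

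**Step 4. Do the windows match?** Service use runs for 3 months after baseline or randomisation: 3 × 52/12 = 13 weeks. Follow-up ends at 14 weeks after randomisation, so 14 − 13 = 1 week is left over. The present record search stops about a week before the last assessment.

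**The case against.** The strongest reply is that the definition is broad where it matters most. A manic or psychotic relapse would ordinarily be a fall in psychosocial functioning, and the wording takes in any such fall however slight. Relapse is also a named secondary outcome, admissions and crisis care are drawn from records, and mood is measured repeatedly. For relapses that reach services, the question is in which table they appear, not whether the data are lost. This stands. A reader might infer from the definition that relapse is excluded; the article does not support that. Relapse is unnamed and depends on judgement where functioning has not visibly declined.

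A reader might also infer that the harms outcome measures the wrong thing. That goes too far: functional deterioration is a relevant harm of a psychological therapy. The definition is incomplete, not misdirected.

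It can be said, too, that the seriousness sentence speaks of events in general and lets participant, clinical service or research team raise one, that ordinary sponsor and ethics governance applies, and that a safety claim is not among the research questions. These points soften the consequence. They do not widen the definition, supply seriousness criteria or remove the filter placed before seriousness review. Nor does the brevity of a journal article explain the gap, because the definition is printed in full and this is not a detail left to a longer document.

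**Conclusion.** The point holds as a matter of wording. The article states a single-domain definition with no threshold. Followed literally, it allows a death, an injury or an act of self-harm to stay out of an outcome that the trial names. It leaves symptomatic worsening to a judgement about functioning, and admissions and crisis episodes unlinked to the harms record. The efficacy analyses are unaffected.

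The size cannot be given as a count. It is tempting to turn the quoted 40 to 60 per cent relapse range into a number of missed relapses among the 36 participants. That would need a period for the rate, which the article does not state, and a proportion of relapses that raters would fail to see as functional decline, for which it offers nothing. No such number should be claimed.

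The conclusion assumes that staff apply the printed definition as it stands, and that no wider definition governs in a document not shown. If there is one, the article should be brought into line with it. The change is worth making because it is cheap and most of the extra data are already being collected.

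**What to change.** 1. Define an adverse event as any untoward occurrence in a randomised participant, whether or not related to the study. Expressly include death, physical injury, self-harm, onset or worsening of mood or psychotic symptoms, and decline in psychosocial functioning.
2. State criteria for seriousness. Record severity and seriousness for every event before relatedness and expectedness are judged. Minor dips can then be reported separately from important events, which a broader definition alone would not achieve.
3. Enter each psychiatric admission and each crisis or home-treatment episode found in the record search as an event, in both arms.
4. Extend that search to the 14-week assessment, so that it covers the whole follow-up. Table 1 already schedules the service-receipt measure at that visit. The 3-month service-use average can stay as defined.

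The cost is a few sentences in the safety section, a cross-entry from data mostly extracted already, about one more week of record search per participant, and more events to log. The change concerns recording and reporting only and leaves clinical care as it is.

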#### Service use and costs

We will approximate costs by counting average service use/month for the 12 months preceding randomisation [19], and the 3 months following randomisation. Service use variables will include number of psychiatric inpatient admissions, days as an inpatient, number of crisis team contacts, and days under the crisis team.

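### Seriousness review is conditional on an event first being considered unexpected and study-related, so serious adverse events are not classified on the same basis in both arms

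*Protocol article*

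**What the plan says.** The section on safety monitoring and adverse event reporting describes four steps.

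1. Adverse events are an outcome: "we will monitor adverse events, defined as any deterioration in psychosocial functioning, irrespective of severity, carefully as one of our outcomes".
2. Every event is recorded: "All adverse events will be reported to the clinical team to ensure adequate care, and will be documented by the study team".
3. A subset goes to a seriousness review: "Events considered by the participant, clinical service or research team to be unexpected and related to the study will be reviewed for seriousness".
4. Expedited reporting follows: "Serious adverse events that are related to the trial will be reported to the trial sponsor and the REC within 15 days".

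Step 3 is the only route to a seriousness review that the article describes.

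Separately, the secondary outcome is service use, "assessed from the medical records for the 12 months preceding entry to the study and the 3 months during the trial". The Service use and costs section lists the variables as "number of psychiatric inpatient admissions, days as an inpatient, number of crisis team contacts, and days under the crisis team". No judgement of cause or expectedness applies to these counts, and they are not limited to one arm.

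Under Data monitoring, the investigators plan no interim analysis or Trial Steering Committee and "will not convene a separate Data Monitoring Committee".

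**The concern.** Whether an event is serious depends on what happened, not on what caused it or whether it was foreseeable. The usual order is to classify seriousness for every event and then to judge relatedness and expectedness, which decide how fast and to whom it is reported. The article reverses this order, with two possible consequences.

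The first is bias. The comparator is routine care alone, so apart from assessments there is little in that arm to which an event could be attributed as study-related. A filter on relatedness therefore works differently by arm, and any count of classified serious events carries that difference whatever the true rates are.

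The second is incomplete reporting. The filter in step 3 is narrower than the duty in step 4, so step 4 can miss events that it is written to catch.

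The study is meant to lead to a larger one, which could inherit both the procedure and a serious-event comparison that cannot be interpreted.

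**Working it through.** There is no figure in the plan to reproduce. The point rests on applying the stated steps to each kind of event.

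**Inputs.** The four steps above; the comparator (Study design: routine care alone); the blinding arrangements (Blinding procedure); the relapse rate (Background: 40 to 60%, no time base); the sample size (36, randomised 1:1, so 36 / 2 = 18 per arm).

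**Step 1: suppose an event is in fact serious, and follow it through the rule.**

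- *Related and unexpected:* reviewed in step 3, reported in step 4. The rule works.
- *Related and expected:* fails the unexpectedness condition, so no seriousness review is described. Step 4 nevertheless covers it, because step 4 asks only for serious and related. The two sentences do not fit together here.
- *Unrelated, expected or not:* no seriousness review is described. Step 4 does not require a report, so expedited reporting is unaffected. But the event is documented without a seriousness label and would be absent from a table of serious events.

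**Step 2: place the arms in these cells.** TAU events fall almost entirely in the unrelated cell. ACT/PE events can fall in any of them. The labelled serious events in the two arms are thus selected by different rules.

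**Step 3: who applies the filter.** The participant, the clinical service or the research team may raise an event. Participants and therapists cannot be blinded. The clinical service is not said to be. Post-randomisation assessors are blind. So some, not all, of those judging relatedness know the allocation.

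**Step 4: how readily an event could be called expected.** With relapse quoted at 40 to 60%, a relapse is an easy event to regard as expected. The article gives no definition of expectedness, so how often this would happen cannot be derived.

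**Step 5: what escapes the filter.** Total documented adverse events (step 2 of the article's procedure) and psychiatric admissions, inpatient days, crisis contacts and crisis days are all available by arm. Not covered by the service-use counts are deaths, medical admissions, and self-harm that leads to neither admission nor crisis contact.

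**Illustration of scale (assumption, not a document figure).** If 25 to 60% of participants had a psychiatric admission in a year at a constant hazard, the 3-month risk is 1 − (1 − p)^(1/4):

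- p = 0.25: 6.9%, × 18 = 1.25 people per arm
- p = 0.40: 12.0%, × 18 = 2.16
- p = 0.60: 20.5%, × 18 = 3.69

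So there would be roughly one to four people admitted per arm, all of whom the service-use outcome would count anyway.

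**The case against.** A reader might infer that harms cannot be compared between the arms at all. The documents do not support that. All adverse events are documented whatever their severity or cause, and admissions and crisis care come from medical records in both arms. An imbalance in psychiatric admissions would be visible in the secondary outcome at the final analysis.

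A reader might also infer that most serious events, and nearly all of those in TAU, would go unclassified. The direction is reasonable, but the article gives no admission or serious-event rate, and the Background figure is relapse without a time frame. The illustration above cannot establish a share.

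Further points in the plan's favour are fair. The filter opens if any one of three parties raises the event, and it refers to the study rather than the therapy, so a TAU event linked to an assessment could pass it. The article may be condensing a fuller procedure, and it does not expressly rule out another route to a seriousness review. The absence of a monitoring committee is stated openly and justified for a small pilot. The scope of the adverse event definition and the details of ascertainment may be left to the full protocol. None of these last matters is part of this point. At this sample size a formal comparison would also be weak: one admission in 18 against four in 18 gives a two-sided Fisher p of about 0.34.

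What remains is that the ordering is stated, not omitted, and that two adjacent sentences set different conditions for related serious events. A fuller procedure elsewhere would not make the published sentences agree. Low power does not excuse the arm-dependent filter either: in a pilot the description of harms matters more than the test.

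**Conclusion.** The point holds in a limited form. Because the seriousness review depends on unexpectedness and relatedness, serious adverse events are not classified on the same basis in the two arms, and a between-arm table of them would be unreliable. Related but expected serious events have no stated route to being found serious, although they fall under the 15-day duty.

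The loss is confined to the serious label, chiefly for events outside psychiatric admission and crisis care, and to the completeness of expedited reporting. The primary outcome, the service-use outcome and the feasibility aims are untouched. The conclusion assumes that the procedure is followed as written and that TAU events are rarely judged study-related. It needs no assumption about event rates. It should be fixed, but it does not undermine the trial.

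**What to change.** Replace the sentence on seriousness review with wording such as:

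> Every documented adverse event in both arms will be classified for seriousness, whatever its relatedness or expectedness. Relatedness and expectedness will then be judged and recorded. Serious adverse events will be tabulated by randomised arm.

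Leave the following sentence, on reporting related serious events within 15 days, unchanged. It then applies to a complete set of serious events.

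The cost is a few more events to classify. No new data source is needed, because all adverse events are already documented and psychiatric admissions are already extracted for the secondary outcome. The classification can also be applied to events already recorded.
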